### Sample size calculation and statistical analysis

In MZL a variety of treatment modalities are used. So far rituximab single agent is the most frequent chemotherapy-free approach used in this entity. Thus, a novel chemotherapy-free approach should be at least as efficient as rituximab monotherapy. In a large randomized trial rituximab monotherapy induced a CR of 55.8% compared to 78.8% for the combination of immunochemotherapy in treatment naïve EMZL subjects. CR rates in splenic MZL are comparable high at about 60%, whereas CR rates in nodal MZL are reported a rare event. As the distribution of subtypes is about 70% EMZL, 20% splenic and 10% nodal MZL, a CR which is better than 56% should at least be achieved by a new chemotherapy-free approach at 12 months after start of therapy.

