For sample size calculation the one-sided one sample exact binomial test was used. According to the above data, the CR for the total group of the different subtypes must be better than 56% 12 months after start of induction therapy. Based on a CR for copanlisib of about 75%, a significance level of 2.5% (because of one-sided test) and a power of 80%, 48 full evaluable patients will be necessary to show that the combination will be a promising candidate for challenging immunochemotherapy. It is expected, that the rate of withdrawal is smaller than 15%. According to these parameters, the study is planned to enroll 56 subjects. The distribution between the sexes is not relevant, because neither incidence of MZL differed between sexes nor clinically outcome measures have been shown to be related to sexes. The primary endpoint will be evaluated 12 months after the last patient recruited has started induction treatment. The primary parameter CR will be evaluated in a modified intention to treat way, which means that all patients for whom the primary endpoint CR is measured at 12 months after start of induction will be included in the analysis of the primary endpoint (core analysis population). This analysis population consists of all eligible patients included in the study who received at least one cycle of treatment. Patients without staging 12 months after start of treatment will be defined as non-responder (CR = ‘NO’). Patients who progress before end of induction therapy will be regarded as treatment failure. No primary end point will be determined for patients who withdraw. These patients will be excluded from the confirmatory data analysis but will be analyzed in a separate exploratory sensitivity analysis of the primary end point.

The decision about the new dual treatment concept of copanlisib in combination with rituximab will be based on the one-sided one sample exact binomial test, using CR ≤ 56% as H0. Thus, claim of success can be done if 36 (75% of 48 patients) or more CR will be observed. Additionally, a one-sided 97.5% confidence interval for CR will be calculated as an effect estimator. Exploratory use of univariate logistic regression models will be performed to investigate the influence of putative risk factors associated with CR. Subgroup analysis in the subtype strata will be performed as further exploratory analysis. All secondary end points will be analyzed exploratory by respective descriptive analysis and 95% confidence intervals.

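### The confirmatory CR analysis has two incompatible denominators: a treated patient who withdraws without month-12 staging is both a non-responder and excluded

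*Protocol article*

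**What the plan says.** All the relevant text is in one paragraph of the protocol article, under Sample size calculation and statistical analysis. It makes four statements about who enters the primary analysis:

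1. The analysis is called modified intention to treat, and "all patients for whom the primary endpoint CR is measured at 12 months after start of induction will be included".
2. The next sentence defines the same population as all eligible patients who had one or more treatment cycles, with no condition on measurement.
3. "Patients without staging 12 months after start of treatment will be defined as non-responder", that is, CR = NO.
4. "No primary end point will be determined for patients who withdraw". "These patients will be excluded from the confirmatory data analysis" and go to an exploratory sensitivity analysis.

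The paragraph also counts progression before the end of induction as treatment failure. The decision uses a one-sided exact binomial test "using CR ≤ 56% as H0", with success claimed at 36 or more CRs, described as 75% of 48 patients. Forty-eight evaluable patients are raised to 56 enrolled to allow for withdrawal below 15%.

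**The concern.** A treated patient who leaves before month 12 has no month-12 staging. Statement 3 keeps that patient in the denominator as a failure, and statement 4 takes the patient out. Statements 1 and 2 conflict in the same way. Withdrawal is neither defined nor distinguished from missing staging, so the text does not settle which rule applies.

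In a single-arm trial tested against a fixed 56%, the denominator is the analysis. Removing unstaged patients whom statement 3 would count as failures can only raise the CR rate. If those patients really are less often in CR, the test also rejects a true null too often.

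**Working it through.** **Inputs** (all from Sample size calculation and statistical analysis): H0 CR 56%, rounded from 55.8% in a randomised trial of rituximab monotherapy; alternative 75%; one-sided alpha 2.5%; 48 evaluable; 56 enrolled; success at 36 or more. Eight withdrawals is the gap 56 − 48, and 8/56 = 14.3%, just inside the planned ceiling of 15%. Every probability below is an exact binomial tail, P(X ≥ r | n, p).

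**The plan's own figure.** With the unrounded null, P(X ≥ 34 | 48, 0.558) = 0.0239 and P(X ≥ 34 | 48, 0.75) = 0.800, so 48 reproduces. With the rounded null, 34 of 48 just misses (0.0255), and the exact cut-off is 35 (0.0120). The stated count of 36 is stricter still (0.0052). That mismatch is a separate matter; here it means error rates must be given for both 35 and 36.

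**Same data, two rules** (8 of 56 withdrawn and unstaged, 36 CRs among the rest):

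| Rule | CR rate | p against 56% | Lower 97.5% limit | Result |
|---|---|---|---|---|
| Excluded | 36/48 = 75.0% | 0.005 | 60.4% | success |
| Counted NO | 36/56 = 64.3% | 0.132 | 50.4% | no success |

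**Range of counts affected.** At n = 56 the exact test needs 40, because P(X ≥ 39 | 56, 0.56) = 0.0259 and P(X ≥ 40 | 56, 0.56) = 0.0130. At n = 48 it needs 35. Every count from 35 to 39 therefore passes under one rule and fails under the other (36 to 39 if the stated count of 36 is used at n = 48).

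**One-sided error under exclusion.** Suppose the true CR rate over all 56 is 56%, so 0.56 × 56 = 31.36 CRs are expected, and 8 withdraw. The rate among the other 48 is (31.36 − 8q)/48, where q is the CR rate the withdrawn patients would have had. The documents give no value for q, so a range is shown:

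| Assumed q | Rate among 48 | Error, stated ≥36 | Error, exact ≥35 |
|---|---|---|---|
| 0 | 31.36/48 = 65.3% | 10.3% | 17.1% |
| 28% (half the null) | 29.12/48 = 60.7% | 2.7% | 5.4% |
| 56% (unrelated to response) | 56.0% | 0.5% | 1.2% |

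With fewer withdrawals, q = 0 and the exact cut-off for each denominator, the error is 4.3% (2 withdrawn), 7.1% (4) and 11.2% (6).

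**Power under the non-responder rule.** If 75% holds over all 56, P(X ≥ 40 | 56, 0.75) = 0.783. If it holds only among 48 staged patients, the overall rate is 0.75 × 48/56 = 64.3% and P(X ≥ 40 | 56, 0.643) = 0.16.

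**The case against.** The strongest defence is that the withdrawal rule is the specific one and names the confirmatory analysis, while the missing-staging rule is general and could cover patients still in the study who were not staged. The move from 48 to 56 fits that reading, and withdrawn patients do get a stated sensitivity analysis. This makes exclusion the likelier intention. It does not remove the conflict: statements 2 and 3 would still be wrong as written for these patients, and the sensitivity analysis is exploratory and does not govern the success claim. Nor is this a detail left to a fuller document, since the article states rules that disagree.

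A reader might infer more than the text supports:

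- **That exclusion inflates the type I error as such.** It does so only if withdrawn patients are less often in CR. If withdrawal is unrelated to response, the error stays below 2.5%.
- **That 17% is the error of this plan.** That figure needs 8 withdrawals, no CR among them and a cut-off of 35. The plan's stated count is 36.
- **That withdrawal means toxicity or lack of benefit.** The article does not say so. Progression during induction already counts as failure, and the Treatment section keeps following patients who discontinue treatment, so withdrawal may be a narrower category such as withdrawn consent. A patient who stops treatment but is staged at month 12 also falls outside the missing-staging rule.
- **That low power is a defect of the present plan.** The 16% arises only if the non-responder rule is adopted and the 75% refers to staged patients alone.

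**Conclusion.** The contradiction stands and needs no assumption about why patients withdraw. The paragraph defines the core population in two ways and treats a withdrawn, unstaged patient in two ways. With 8 of 56 withdrawn, the result turns on the rule for any count from 35 to 39 CRs.

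The bias is conditional. Against the plan's own non-responder rule, exclusion raises the CR rate whenever a withdrawn patient is unstaged and anyone is in CR. Its effect on the one-sided error, at 8 withdrawals and the stated count of 36, runs from no inflation (withdrawal unrelated to response), through about 2.7% (half the null CR rate, assumed), to 10.3% (none would be in CR). At the exact cut-off of 35 the last two are 5.4% and 17.1%. Because this is the trial's only confirmatory test, the text should be corrected before the primary analysis.

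**What to change.** - Use one confirmatory population: all eligible patients who received at least one cycle. Drop the condition that CR has been measured.
- Count every patient in it without a documented CR at month 12, withdrawals included, as CR = NO.
- Define withdrawal, and make the analysis that leaves withdrawn patients out the exploratory sensitivity analysis.
- Replace the fixed count of 36 with the exact critical count for the actual denominator. At 56 patients that is 40; carrying 36 over would give a one-sided error of 13.2%.
- State whether the 75% refers to all treated patients or only to those staged, and restate power: about 78% at n = 56 in the first case, about 16% in the second with 48 staged. The second would call for a review of the sample size.

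The cost is more than wording. The reported CR rate will be lower if anyone withdraws, and the stated power will be less favourable, much less so if the 75% was meant for staged patients only. No extra data collection is needed.

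### The fixed success count of 36 complete responses is not the cut-off of the planned exact test: at 48 patients it cuts power to 58%, and at 56 it raises the type I error to 13%

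*Protocol article*

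**What the plan says.** All of this stands in the protocol article, section Sample size calculation and statistical analysis.

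- **Design:** "For sample size calculation the one-sided one sample exact binomial test was used". The assumptions are a CR rate of about 75% for the new treatment, a one-sided level of 2.5% and 80% power, from which "48 full evaluable patients will be necessary". Withdrawal is expected to stay below 15%, so "the study is planned to enroll 56 subjects".
- **Decision:** it rests on the "one-sided one sample exact binomial test, using CR ≤ 56% as H0".
- **Count:** the next sentence turns this into a number: "Thus, claim of success can be done if 36 (75% of 48 patients) or more CR will be observed".
- **Analysed number:** patients without staging at 12 months stay in the analysis as non-responders, and patients who withdraw are left out of the confirmatory analysis. The analysed number is therefore not fixed at 48. No count is given for any other number.

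**The concern.** The success count is presented as a consequence of the exact test, but the parenthesis shows that it is the assumed alternative rate times the planned number, 0.75 × 48 = 36. A critical value comes from the null rate and the significance level; the alternative plays no part in it. A rule that requires the observed rate to reach the assumed true rate fails often even when that assumption is correct.

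The count also carries no adjustment for the number analysed. If 36 is kept while the denominator grows towards 56, the observed rate needed for success falls from 75% to 64.3%, and control of the type I error is lost.

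This is the only confirmatory decision of a single-arm trial. With two rules that can give opposite answers, the choice between them could be made after the data are known.

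**Working it through.** **Inputs** (all from the section Sample size calculation and statistical analysis): null rate p0 = 0.56; alternative p1 = 0.75; one-sided alpha = 0.025; target power 0.80; 48 evaluable patients; 56 enrolled; stated count 36. The same section gives the source of the null rate, unrounded, as 55.8%.

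**Formulas.** For X ~ Bin(N, p), the upper tail is P(X ≥ r | N, p) = Σ from k = r to N of C(N,k) p^k (1−p)^(N−k). The exact cut-off is the smallest r with P(X ≥ r | N, p0) ≤ 0.025. Power is P(X ≥ r | N, p1).

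**1. The plan's own sample size.** With p0 = 0.558, the smallest N that meets both targets is 48, with cut-off 34: alpha 0.0239, power 0.8001. So the 48 is reproduced, with a cut-off of 34. With p0 = 0.56 as written in the hypothesis, 34/48 just misses (alpha 0.0255), and the smallest N is 51 with cut-off 36 (alpha 0.0236, power 0.815).

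**2. Cut-offs at N = 48.**

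| Required CRs | Alpha, p0 = 0.56 | Alpha, p0 = 0.558 | Power at 75% |
|---|---|---|---|
| 34 | 0.0255 | 0.0239 | 0.800 |
| 35 | 0.0120 | 0.0112 | 0.699 |
| 36 | 0.0052 | 0.0048 | 0.577 |

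The exact cut-off is 35 with a null of 56% and 34 with 55.8%. It is 36 with neither. Under the rule of 36, the true CR rate would have to be 78.9% for 80% power.

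**3. The count of 36 against the exact cut-off as N changes** (p0 = 0.56).

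| N | Exact cut-off | Alpha of exact rule | Power of exact rule | Alpha of ≥ 36 |
|---|---|---|---|---|
| 48 | 35 | 0.012 | 0.699 | 0.005 |
| 49 | 35 | 0.020 | 0.775 | 0.009 |
| 50 | 36 | 0.015 | 0.748 | 0.015 |
| 51 | 36 | 0.024 | 0.815 | 0.024 |
| 52 | 37 | 0.018 | 0.791 | 0.036 |
| 53 | 38 | 0.014 | 0.766 | 0.052 |
| 54 | 38 | 0.022 | 0.828 | 0.073 |
| 55 | 39 | 0.017 | 0.806 | 0.100 |
| 56 | 40 | 0.013 | 0.783 | 0.132 |

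With p0 = 0.558, the type I error of 36/56 is still 12.6%.

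**4. Results on which the two rules disagree** (exact one-sided 97.5% lower bound).

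- 35/48 = 72.9%: p = 0.012, lower bound 58.2%. The test rejects; the count says no success.
- 36/56 = 64.3%: p = 0.132, lower bound 50.4%. The count says success; the test does not reject, and the planned confidence interval includes rates below 56%.

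**The case against.** The test is named before the count, and the parenthesis ties 36 to 48 patients. One can therefore read the test as the governing rule and 36 as an illustration for N = 48. On that reading 36/56 is not a success and no type I error inflation arises. The wording also makes 36 a sufficient condition, and at N = 48 it is one (p = 0.005). This reading is possible, but the text does not secure it: the count is given as what follows from the test, and as an illustration for 48 it is still wrong, because 35 is enough.

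The 13% is an extreme. It needs all 56 patients in the analysis, with no exclusions. With five to eight patients lost (N = 51 to 48), even a fixed 36 stays at or below 2.4%. This is correct. However, the plan expects fewer than 15% withdrawals and keeps unstaged patients in the denominator, so 52 or more is within reach, and inflation begins there.

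Not all of the lost power is due to the count. With the null at 56%, the correct test at 48 patients has 70% power, so the count costs about 12 points (69.9% to 57.7%). The remaining 10 points or so come from rounding 55.8% up to 56%. Only with 55.8% as the null does the count take power from 80% to 58%. This stands, and it means that correcting the count does not by itself restore 80% at 48 patients.

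**Conclusion.** The point holds: the stated count is wrong as a consequence of the planned test. At 48 patients it is one CR too strict (two if the null is 55.8%). It gives a type I error of 0.5% and a power of 57.7%, so the trial would miss its criterion with probability 42% even if the true CR rate were 75%. This part depends only on 36 being used as the cut-off at 48. If 36 is also applied whatever the number analysed, the type I error is 3.6% at 52 patients and rises to 13.2% at 56, the case with no exclusions. The figures assume independent patients and the rates stated in the plan; moving the null between 55.8% and 56% does not change the conclusion. It should be corrected before the primary analysis because it concerns the claim of success itself.

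**What to change.** Delete the fixed count and state one rule, for example: success is claimed if the one-sided exact binomial p-value against a CR rate of 56%, at the actual number of patients in the confirmatory population, is at most 0.025. Add the cut-offs as illustration: 35/48, 35/49, 36/50, 36/51, 37/52, 38/53, 38/54, 39/55, 40/56.

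In the same edit, confirm whether the null is 56% or 55.8%. The list above is for 56%; with 55.8% the cut-offs are 34/48 and 39/56. If 56% stays, report that 48 analysed patients give 70% power and that 51 is the smallest number reaching 80%, which 56 enrolled patients can still supply if no more than five are excluded. Power then still dips slightly below 80% at some numbers because the test is discrete (for example 78% at 56).

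The cost is one sentence and a small table in the protocol and the SAP. No additional patients or data are needed to correct the rule.

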### Biosampling program

The study includes a translational biosampling program which will serve as a platform for future research projects. The stored biospecimen program is a collection of serum, bone marrow and DNA specimens. Based on the study design, six eligible time points with sample collection prior to treatment, at the end of induction, at the primary endpoint (month 12), at the end of copanlisib treatment (month 20), at maintenance completion visit and in case of progression are defined (Fig. 3).

**Fig. 3 Fig3:**
[figure not shown]
Timeline of biomarker analyses of the COUP-1 trial

## Discussion

We describe here an open-label, multicentric phase II trial to confirm the efficacy and safety of the combination of rituximab with copanlisib in MZL patients, who are either treatment naive or have relapsed/refractory disease. In this mostly elderly patient population, the development of chemotherapy-free approaches is of particular interest. However, complete response rates shown with target molecules given as a single agent are usual low and might be explained to the activation of additional pathways in resistant cases [22]. Thereby there is an urgent need to test combinations of compounds with complementary mode of action, ensuring long-lasting eradication of MZL cells. Indeed, combination testing deciphered several compounds, among them rituximab, that synergize with copanlisib in B-cell lymphoma models [23].

The PI3Kδ inhibitor idelalisib was the first in its class to receive FDA approval in relapsed follicular lymphoma based on an overall response rate of 57% (CR 7%) in double refractory patients. Similar results were reported for relapsed MZL patients (OR 47%, no CR) [24]. However, early enthusiasm for this agent went down due to its toxicity profile and the drug subsequently gained a black box warning for adverse events such as hepatotoxicity, colitis, pneumonitis, and increased risk of opportunistic infections. Unexpected aggravation of adverse events in combined applications of idelalisib, including rituximab, even culminated in premature termination of trials and subsequently resulted in a restriction of its use despite the release of recommendations for the management of toxicity associated with idelalisib [25–27]. Copanlisib shows higher potency against all four PI3K class I isoforms and a more preferential targeting of the PI3Kα compared to idelalisib and actually seems to have a more favorable safety profile, raising the possibility that side effects of selective PI3Kδ inhibition might be avoided. The reported main side effects of copanlisib are mostly infusion-related including transient hyperglycemia, which is an expected on-target effect of PI3Kα inhibition that is related to insulin-receptor signaling [28, 29]. Besides hyperglycemia, most common reported higher treatment-related adverse events are transient hypertension and neutropenia. Regarding the unique side effect profile of copanlisib, recommendations on optimal management of copanlisib associated adverse events have been recently published and will help to manage safe drug administration [30].

Based on the known activity and the favorable toxicity profile of rituximab as single agent and the promising efficacy results of copanlisib, the concept of this chemotherapy-free treatment approach is highly attractive and will help to define the role of this combination in MZL patients, aiming at challenging immmunochemotherapy. It will further help to evaluate the feasibility of rituximab/copanlisib maintenance therapy after induction in patients with MZL.

## Data Availability

Not applicable.

## Abbreviations

ADCC: Antibody dependent cell-mediated cytotoxicity
ADP: Antibody dependent phagocytosis
BTK: Bruton tyrosine kinase
CD: Cluster of differentiation
CDC: Complement-dependent cytotoxicity
CNS: Central nervous system
CR: Complete response
CT: Computed tomography
CTCAE: Common Terminology Criteria for Adverse Events
DSMC: Data Safety Monitoring Committee
ECOG: Eastern Cooperative Oncology Group
EMZL: Extranodal marginal zone lymphoma
Fab: Fragment antigen-binding
FACT-Lym: Functional Assessment of Cancer Treatment-Lymphoma
Fc: Fragment crystallizable
FDA: Food and Drug Administration
GELA: Groupe d'Etude des Lymphomes de l'Adulte
GFR: Glomerular filtration rate
HbA1c: Hemoglobin A1c
H0: Null hypothesis
IELSG: International Extranodal Lymphoma Study Group
NMZL: Nodal marginal zone lymphoma
MRI: Magnetic resonance imaging
MZL: Marginal zone lymphoma
OR: Overall response
OS: Overall survival
PIP2: Phosphatidylinositol 4,5-bisphosphonate
PIP3: Phosphatidylinositol 3,4,5-bisphosphonate
PI3K: Phosphatidylinositol-3-kinase
PFS: Progression free survival
PR: Partial response
SMZL: Splenic marginal zone lymphoma
WHO: World Health Organization
